### Sample Size and Power Considerations

Because this protocol involves model development, validation, and implementation feasibility, the planned sample size was based on expected cohort availability and anticipated outcome events rather than a conventional hypothesis-testing formula. The sample size determination for this study is primarily driven by the second aim, which focuses on validating the predictive model for CSPH. On the basis of preliminary data and published estimates, we anticipate enrolling approximately 600 patients with PBC across participating sites [7]. This cohort size reflects the expected availability of retrospective and prospective data within the study time frame and ensures adequate representation of key subgroups, including patients with AIH overlap and MASH [19,20].

On the basis of prior PBC cohorts, the prevalence of portal hypertension or CSPH in hepatology referral populations has been reported to range from approximately 24% to 47% depending on disease stage and case mix [25,26]. With a projected sample of 600 participants, this corresponds to an estimated 144 to 282 CSPH events, which provides a sufficient number of outcome events to support model development and validation and evaluate improvements in model discrimination relative to established criteria such as Baveno VII.

In addition, sample size considerations accounted for model complexity. Current methodological guidance for prediction modeling recommends ensuring an adequate number of outcome events relative to the number of predictor parameters to reduce the risk of model overfitting. The anticipated event counts in this cohort are expected to support the planned set of candidate predictors while maintaining an appropriate events-per-predictor ratio for stable model estimation [27].

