### AI Model Development and Validation

The predictive model will be developed using a prespecified machine learning pipeline. Candidate predictors will include longitudinal biochemical markers, platelet count, LSM, SSM, symptom scores, treatment response status, and relevant comorbidities. Features will be selected based on clinical relevance, data availability, and model stability, with highly collinear or sparsely available variables excluded or combined where appropriate.

The dataset will be divided into training, internal validation, and held-out testing subsets at the patient level to avoid data leakage. Model development will use gradient-boosted ensemble algorithms, with hyperparameters tuned within the training set using cross-validation. External validation will be performed using data from at least one participating site not used during model training where feasible.

Class imbalance will be addressed using strategies applied only within the training data, including class weighting or resampling approaches as appropriate. SHAP values will be generated to provide both patient- and cohort-level feature contributions. Model updating will not be performed during initial validation; if performance drift or poor calibration is observed during prospective deployment, recalibration or updating will be conducted using prespecified procedures and reported transparently.

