### Statistical Analysis

For the first aim, longitudinal PROs and biochemical markers will be analyzed using mixed-effects models to account for within-subject correlation and repeated measures over time. These models will assess the responsiveness of integrated symptom indexes to changes in biochemical progression or regression, whereas calibration of the AIm-PBC disease activity index will be evaluated against established risk scores such as UK-PBC and GLOBE using the calibration slope, intercept, and Brier score. Discrimination will be quantified through the AUROC, and visualizations of SHAP values will be examined to confirm clinical interpretability.

For the second aim, the predictive model for CSPH complications will be developed using gradient-boosted ensemble algorithms chosen for their robustness in handling heterogeneous data. Model performance will be assessed through the AUROC for discrimination and calibration plots for agreement between predicted and observed outcomes. Clinical utility will be evaluated using decision curve analysis and net reclassification improvement to determine whether the composite model offers meaningful improvement over existing criteria. Comparative analyses will use DeLong tests to assess differences in AUROC between models, and subgroup analyses will be conducted to evaluate fairness and consistency across patients with AIH overlap and MASH. Ablation studies will quantify the incremental value of individual predictors, particularly SSM, by systematically removing variables and observing changes in performance.

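### Training-set class weighting or resampling, with no stated return to the natural event rate before validation, can inflate predicted risks in the Aim 2 calibration, decision-curve and reclassification results

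*Protocol article*

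**What the plan says.** The section AI Model Development and Validation of the protocol article states: "Class imbalance will be addressed using strategies applied only within the training data, including class weighting or resampling approaches as appropriate". The weighting or resampling scheme and the target ratio are not given. The same section says "Model updating will not be performed during initial validation". That sentence continues: "if performance drift or poor calibration is observed during prospective deployment, recalibration or updating will be conducted using prespecified procedures and reported transparently".

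The section Statistical Analysis assesses the Aim 2 model by AUROC and by "calibration plots for agreement between predicted and observed outcomes". It adds decision curve analysis and net reclassification improvement, with DeLong tests for differences in AUROC. Under Outcomes, AUROC quantifies the Aim 2 primary outcome, and calibration and clinical utility are additional measures.

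Sample Size and Power Considerations says that the prevalence of portal hypertension or CSPH "has been reported to range from approximately 24% to 47% depending on disease stage and case mix". Under Interventions, clinicians see risk cards and dual-threshold triage cues. Under Harms, the tool supplies risk estimates in the simulation.

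**The concern.** Restricting the balancing step to the training data is right for preventing leakage. It also means that a model fitted at an artificial event rate is judged on data at the natural rate. Balancing raises the predicted odds of every patient by roughly a constant factor. Unless that factor is removed, the model overpredicts in validation, and the article names no step between fitting and validation that removes it.

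Ranking is hardly touched, so AUROC will not reveal the problem. Three of the stated Aim 2 measures do read absolute risk: calibration plots, decision curves and net reclassification improvement. In these the model could look worse than it is, or patients could be reclassified against the Baveno VII criteria for reasons unrelated to the predictors. The same probabilities go to clinicians in the simulation and at the start of the pilot.

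**Working it through.** **Inputs.** From Sample Size and Power Considerations: 600 participants and prevalence of 24% to 47%. From Results: expected AUROC of at least 0.85. Assumptions of this check: full 1:1 balancing (the article fixes no ratio), a binormal score with AUROC exactly 0.85, and, for the boosting check, 420 training patients (70% of 600).

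**The plan's own figure.** 600 × 0.24 = 144 and 600 × 0.47 = 282. Both match "this corresponds to an estimated 144 to 282 CSPH events". At these rates the imbalance is moderate at most.

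**Shift in predicted risk.** Balancing to 1:1 at prevalence p multiplies the predicted odds by k = (1 − p)/p, a logit shift of ln k. A true risk q is then shown as qk/(1 − q + qk).

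| Prevalence | k | ln k | True 10% shown as | True 20% shown as |
|---|---|---|---|---|
| 24% | 0.76/0.24 = 3.17 | +1.15 | 26% | 44% |
| 35.5% (midpoint) | 0.645/0.355 = 1.82 | +0.60 | 17% | 31% |
| 47% | 0.53/0.47 = 1.13 | +0.12 | 11% | 22% |

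Example at 24%: the odds for 10% are 0.1/0.9 = 0.111; 0.111 × 3.17 = 0.352; 0.352/1.352 = 26%.

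**Other ratios and rates.** With a milder event weight of 1.5 (assumed), the shift is ln 1.5 = +0.41 and a true 10% is shown as 0.1667/1.1667 = 14%. For an outcome with an assumed rate of 10%, full balancing gives k = 0.9/0.1 = 9, a shift of +2.20, and a true 10% is shown as 50%. The documents give no rate for incident complications.

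**Effect on the performance measures** (binormal model, 1,000,000 draws; each cell reads natural rate → balanced):

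| Prevalence | Mean prediction | Brier score | Net benefit, 20% threshold | Net benefit, 30% threshold |
|---|---|---|---|---|
| 24% | 24.0% → 40.5% | 0.123 → 0.158 | 0.141 → 0.118 | 0.112 → 0.074 |
| 35.5% | 35.5% → 44.6% | 0.147 → 0.158 | 0.250 → 0.244 | 0.210 → 0.200 |
| 47% | 47.0% → 48.9% | 0.158 → 0.158 | 0.371 → 0.371 | 0.326 → 0.325 |

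At 24% the ratio of observed to expected events falls to 0.24/0.405 = 0.59. The thresholds are illustrative, since the article gives none. Net reclassification improvement was not computed because it depends on the cut-offs, but an upward shift moves events and non-events alike across any fixed cut-off.

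**Gradient-boosting check** (simulated data, 40 repeats, unweighted against balanced weights). At 24%: AUROC 0.815 against 0.818, mean predicted risk 23.9% against 37.9%. At 47%: AUROC 0.825 against 0.825, mean predicted risk 47.2% against 48.7%. In this check, weighting gained essentially no discrimination.

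**The case against.** The case for the plan has five parts.

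- **The amount of balancing is open.** The wording leaves the choice of approach to what is appropriate and sets no ratio, so little weighting might be applied. A reader might infer that the model is miscalibrated by construction. The documents do not support that, because the figures above need substantial balancing. What remains is that the text commits to addressing imbalance and states no correction.
- **There is a recalibration provision.** A reader might infer that nothing ever corrects the distortion. That is not so: poor calibration seen in prospective deployment triggers recalibration or updating. The provision comes too late for the initial validation results, the simulation and the start of the pilot.
- **A correction within fitting is not forbidden.** Returning predictions to the natural rate could be part of the prespecified pipeline, and a condensed article may omit such detail. This stands as a reason for moderation. The article does, however, state the step that creates the shift and a rule that could be read as barring its removal.
- **The stated prevalence does not cover every target.** The 24% to 47% refers to portal hypertension or CSPH. The Aim 2 outcome also includes early complications, which may be rarer, so a provision for imbalance is not plainly pointless. For a rarer outcome, though, uncorrected balancing does more harm.
- **The primary measure is safe.** A reader might infer that the comparison with Baveno VII as a whole is undermined. AUROC depends on ranking, so it and the DeLong tests are not materially affected. Triage cut-offs chosen on the model's own score would also absorb a uniform shift, and the table under Study Design says that Phase 2 will refine thresholds. Displayed probabilities and decision curves would still be affected.

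**Conclusion.** The point holds conditionally. If classes are substantially balanced in training and no correction is made, the Aim 2 calibration plots, decision curves and net reclassification improvement will be distorted, as will the risk estimates shown in the simulation and early in the pilot.

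Under 1:1 balancing the distortion is large at 24% prevalence, moderate at mid-range and negligible at 47%. It would therefore be wrong to describe it as uniform over the plan's range. The shifts follow from the stated prevalences and the assumed ratio. The Brier score and net benefit figures also rest on the binormal model at AUROC 0.85. Near 47% the step does almost no harm, but it also does almost nothing. The change should be made before model fitting; it does not call the primary discrimination analysis into question.

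**What to change.** For the CSPH risk model, replace the class-imbalance sentence with a statement that the model is trained at the natural event rate, without weighting or resampling.

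If weighting or resampling is kept, for example for a rarer complication, add that predictions are recalibrated to the natural event rate on the internal validation subset before the held-out test is opened. State that this recalibration is part of model fitting and is not the updating that is ruled out during initial validation.

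The cost is one or two reworded sentences. No further data are needed, and the Results section says that neither recruitment nor analysis had begun at submission. The boosting check suggests no material loss of AUROC from leaving the weighting out.

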### Statistical Analysis

For the first aim, longitudinal PROs and biochemical markers will be analyzed using mixed-effects models to account for within-subject correlation and repeated measures over time. These models will assess the responsiveness of integrated symptom indexes to changes in biochemical progression or regression, whereas calibration of the AIm-PBC disease activity index will be evaluated against established risk scores such as UK-PBC and GLOBE using the calibration slope, intercept, and Brier score. Discrimination will be quantified through the AUROC, and visualizations of SHAP values will be examined to confirm clinical interpretability.

For the second aim, the predictive model for CSPH complications will be developed using gradient-boosted ensemble algorithms chosen for their robustness in handling heterogeneous data. Model performance will be assessed through the AUROC for discrimination and calibration plots for agreement between predicted and observed outcomes. Clinical utility will be evaluated using decision curve analysis and net reclassification improvement to determine whether the composite model offers meaningful improvement over existing criteria. Comparative analyses will use DeLong tests to assess differences in AUROC between models, and subgroup analyses will be conducted to evaluate fairness and consistency across patients with AIH overlap and MASH. Ablation studies will quantify the incremental value of individual predictors, particularly SSM, by systematically removing variables and observing changes in performance.

For the third aim, implementation outcomes will be analyzed using both descriptive and inferential methods. Usability scores from the System Usability Scale (Multimedia Appendix 1), clinician trust scores from the AI trust scale adapted for AIm-PBC (Multimedia Appendix 2), and cognitive load measures from the National Aeronautics and Space Administration Task Load Index (Multimedia Appendix 3) will be summarized and compared between CDS-assisted and usual care conditions. Decision accuracy and decision time will be analyzed using 2-tailed paired *t* tests within the randomized crossover simulation, whereas clinician adherence to guideline-concordant care pathways will be evaluated using within-clinician comparisons across study phases. Feasibility indicators, such as recruitment and completion rates, will be reported as proportions with CIs. Qualitative debriefing interviews will be analyzed to explore clinician perceptions of usability, workflow integration, trust, and barriers to implementation (Multimedia Appendix 4). Fairness metrics, including AUROC parity gaps across demographic and clinical subgroups, will be calculated to ensure equitable performance of the CDS tool.

All analyses will be conducted using validated statistical software packages in R (R Foundation for Statistical Computing) and Python (Python Software Foundation), with significance thresholds set at a 2-sided α value of .05. Missing data will be addressed through multiple imputation techniques, and sensitivity analyses will be performed to confirm the robustness of the findings.

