## Introduction

### Background

Despite advances in primary biliary cholangitis (PBC) therapy, significant gaps persist in monitoring disease activity, predicting complications, and delivering guideline-concordant care [1-4]. Current management strategies rely heavily on biochemical markers such as alkaline phosphatase (ALP) and bilirubin, which often fail to capture dynamic symptom fluctuations or early progression toward clinically significant portal hypertension (CSPH) [5,6]. This limitation delays timely intervention and contributes to morbidity [7].

Risk stratification for portal hypertension, a complication of PBC, remains particularly challenging [8]. Invasive procedures such as endoscopy are frequently used for variceal screening, yet these approaches are resource intensive and carry procedural risks [2,4]. Noninvasive surrogates, including liver stiffness measurement (LSM) and spleen stiffness measurement (SSM), have demonstrated promise in predicting CSPH and reducing unnecessary endoscopies [2,4,9]. However, these modalities are rarely integrated with longitudinal biochemical data or patient-reported outcomes (PROs), leaving clinicians without a comprehensive, real-time view of disease trajectory [10]. Even when risk is identified, translating insights into action remains challenging. Clinicians face cognitive overload and workflow fragmentation, leading to missed opportunities for guideline-based interventions such as pruritus step therapy, bone health management, and CSPH screening [3].

Symptom burden represents another critical dimension of PBC care. Validated instruments such as the Worst Itch Numeric Rating Scale (WI-NRS) and PBC-40 provide reliable measures of symptom severity [10,11]. Similarly to risk stratification tools, symptom burden tools are underused in routine practice and seldom incorporated into predictive models.

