### Outcomes

The primary outcome for the first aim will be the performance of the AIm-PBC disease activity index compared to conventional monitoring strategies. This will be assessed through its calibration against established risk scores such as UK-PBC and GLOBE [22,23], as well as its responsiveness to clinically meaningful changes in disease activity. The ability of the integrated symptom indexes to correlate with biochemical progression or regression will also be evaluated, providing insights into whether the inclusion of PROs enhances the sensitivity of disease monitoring. Explainability will be measured via the interpretability of SHAP-based visualizations and their perceived clinical utility during clinician evaluations.

For the second aim, the primary outcome will be the discriminatory ability of the multi-signal predictive model to identify patients at high risk of CSPH and early complications such as variceal hemorrhage or ascites. This will be quantified using the area under the receiver operating characteristic curve (AUROC), with additional measures of calibration and clinical utility assessed through decision curve analysis and net reclassification improvement. Comparative analyses will determine whether the composite model outperforms single-modality rules and consensus criteria such as Baveno VII, and subgroup analyses will explore performance consistency across patients with AIH overlap and MASH.

For the third aim, the primary outcome will be the effectiveness and usability of the EHR-integrated CDS prototype. Effectiveness will be measured via improvements in clinician adherence to guideline-concordant care pathways, including pruritus management, bone health interventions, and risk-based endoscopy referrals. Usability will be assessed using the System Usability Scale, with a target score of 70 or higher, and cognitive load will be evaluated using the NASA-Task Load Index. Clinician trust in the AI system will be measured through the AI trust scale, whereas decision accuracy and decision time will be compared between CDS-assisted and usual care conditions during the randomized crossover simulation. Feasibility indicators, including recruitment and completion rates, will be monitored during the pragmatic pilot phase.

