## Discussion

### Principal Results

This protocol describes a multiphase study aimed at improving the management of PBC through an explainable AI framework. The anticipated results include a dynamic disease activity index that integrates biochemical, elastography, and patient-reported data, offering superior responsiveness and calibration compared to conventional monitoring. The predictive model is expected to achieve high discrimination for CSPH and outperform existing criteria, reducing unnecessary endoscopies while maintaining patient safety. Finally, the CDS prototype is designed to enhance clinician adherence to guideline-based care, improve decision accuracy, and reduce cognitive load, with usability and trust scores meeting or exceeding established benchmarks.

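### The Aim 1 analyses use conventional monitoring as their reference, so as written they cannot show that the activity index is better than conventional monitoring

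*Protocol article*

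**What the plan says.** Outcomes sets a comparative primary outcome for the first aim: "The primary outcome for the first aim will be the performance of the AIm-PBC disease activity index compared to conventional monitoring strategies". It is to be judged by calibration against UK-PBC and GLOBE, "as well as its responsiveness to clinically meaningful changes in disease activity". A further item follows for the symptom component: "The ability of the integrated symptom indexes to correlate with biochemical progression or regression will also be evaluated". Outcomes says this item will shed light on whether adding PROs makes monitoring more sensitive.

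Statistical Analysis makes two references operational for this aim. The mixed models carry the first: "These models will assess the responsiveness of integrated symptom indexes to changes in biochemical progression or regression". The second is for the index itself: "calibration of the AIm-PBC disease activity index will be evaluated against established risk scores such as UK-PBC and GLOBE", by slope, intercept and Brier score. An AUROC is added without saying for which outcome.

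On existing practice, Background says: "Current management strategies rely heavily on biochemical markers such as alkaline phosphatase (ALP) and bilirubin". Comparison With Prior Work adds UK-PBC and GLOBE to biochemistry as the established approach. Interventions lists monthly biochemistry, LSM and SSM, and PROs as inputs of the index. Principal Results describes the anticipated index as "offering superior responsiveness and calibration compared to conventional monitoring".

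**The concern.** A claim that a new measure monitors disease better than the usual one needs a third quantity against which both are judged. Here the quantities made operational are the usual measures themselves. Followed as written, Aim 1 could report a well-calibrated index and a symptom score that moves with laboratory values, and both results could be read as support for the superiority statement. Neither would show that PROs and elastography improve on ALP, bilirubin or the existing scores.

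The PRO item has a related difficulty. Background argues for PROs because biochemistry misses symptom fluctuation. On that premise, correlation between PROs and biochemistry does not by itself say whether PROs add sensitivity.

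**Working it through.** **The plan's own figure.** The only size calculation is for Aim 2: 600 × 0.24 = 144 and 600 × 0.47 = 282 CSPH events, as stated under Sample Size and Power Considerations. It reproduces exactly. No figure is given for Aim 1 responsiveness, so none is affected.

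**Claim against analysis.**

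| Element of the Aim 1 claim | Reference in Statistical Analysis | What the article says that reference is |
|---|---|---|
| Responsiveness of the activity index | None stated for the index; symptom indexes are related to biochemical change | Conventional monitoring (Background) and an index input (Interventions) |
| Calibration of the activity index | UK-PBC and GLOBE | Established approach (Comparison With Prior Work) |
| Discrimination | AUROC, outcome not named | Not stated |
| Comparison with conventional monitoring | No head-to-head responsiveness analysis stated | Not stated |

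In the first two rows the best attainable result is perfect agreement with the comparator, which is equality and not superiority.

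**Illustration 1: a composite containing biochemistry.** Assume index = wB + (1−w)S, where B is standardised biochemical change and S is independent standardised noise. Then corr(index, B) = w/√(w² + (1−w)²).

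- w = 0.3: 0.3/√(0.09 + 0.49) = 0.39
- w = 0.5: 0.5/√(0.25 + 0.25) = 0.71
- w = 0.7: 0.7/√(0.49 + 0.09) = 0.92
- w = 0: 0

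B correlates 1.00 with itself. A composite with a worthless symptom part would therefore look responsive to a biochemical yardstick, yet could not beat biochemistry on it. The weights are assumptions. The result applies only to an index that contains biochemistry, as the activity index does. It does not apply to a symptom index made of PROs alone (w = 0).

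**Illustration 2: the choice of reference reverses the answer.** Assume that biochemistry and the other components each load λ on a latent disease activity and are weighted equally. The event is the top quartile of the reference (simulation, n = 400,000).

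| Reference | λ | AUROC, index | AUROC, biochemistry | AUROC, non-biochemical part alone |
|---|---|---|---|---|
| Latent activity | 0.5 | 0.81 | 0.74 | not run |
| Latent activity | 0.7 | 0.90 | 0.84 | not run |
| Biochemical change | 0.5 | 0.89 | 1.00 | 0.62 |
| Biochemical change | 0.7 | 0.93 | 1.00 | 0.74 |

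The same index wins on an independent reference and loses on the biochemical one. The last column shows that a PRO-only symptom index fares no better against a comparator that is perfect by definition.

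**The case against.** The strongest objection concerns the object of the quoted sentence. It is about symptom indexes, and the article keeps these apart from the activity index in both Outcomes and Statistical Analysis. A reader might infer that the activity index's responsiveness is itself anchored to biochemical change and is therefore circular. The documents do not say so. Outcomes gives the index a different, undefined anchor, and nowhere are the symptom indexes said to contain laboratory values. This stands, and it confines Illustration 1 to the activity index. It does not remove the mismatch, because Statistical Analysis then holds no responsiveness analysis of the index at all.

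A reader might also infer that superiority cannot be tested in this study, or that the analysis must end in one of two uninformative answers. Both go too far. No test of biochemistry against itself is written. Data Collection tracks varices, ascites and encephalopathy over 24 months, and an analysis plan not shown may define the anchor. The limit applies to the analyses as written.

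Nor does high PRO–biochemistry correlation prove redundancy. The itch scale is taken twice daily and laboratory values monthly, so a correlated PRO could still signal earlier. The correlation is an ordinary construct-validity check.

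A demand for dated treatment starts as covariates is weakly supported: second-line therapy class is already recorded as a covariate and the data come from EHRs.

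Finally, Principal Results states an expectation and not a formal superiority test. That is true, but the primary outcome in Outcomes is itself worded as a comparison.

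**Conclusion.** The point holds in this form: the Aim 1 analyses do not match the Aim 1 primary outcome or the superiority that is anticipated. The references chosen (biochemical change, UK-PBC and GLOBE) are what the article describes as conventional monitoring, and the AUROC has no stated target. This is a stated choice of reference that cannot answer the stated question, and so more than detail left to a fuller document. The direction of the fault follows from the text alone. Its numerical size rests on assumed weights and loadings and is illustrative. No alpha level, sample size or event count changes.

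**What to change.** Reconcile Outcomes, Statistical Analysis and Principal Results as follows.

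1. Name a reference for Aim 1 that is independent of the comparator and of the inputs at the time of scoring. The primary choice is the clinical outcomes already tracked over 24 months. State it as the target of the AUROC too.
2. On that reference, compare ALP and bilirubin trajectories, and UK-PBC and GLOBE, head to head with the full index in the same patients, and report the increment.
3. Use later elastography change only as a supportive anchor, adjusted for the LSM or SSM value at scoring. Those values are index inputs, so unadjusted change is coupled to the index.
4. Keep the correlation of PROs with biochemistry as a construct-validity check, and remove the suggestion that it shows added sensitivity.
5. Keep calibration against UK-PBC and GLOBE, labelled as agreement with existing scores.

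The cost is mainly analysis wording. The data are already planned, and the article reports that recruitment had not begun. The downside is precision. Clinical events may be sparse (the 144 to 282 figure is based on CSPH prevalence and does not count complications over 24 months), and they overlap with the Aim 2 outcome. If they prove too few, drop the superiority wording in Principal Results, and the matching expectation of greater responsiveness in Results, and report Aim 1 as agreement with existing scores.
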